## Abstract

The Mediterranean diet has demonstrated efficacy for improving cardiovascular and cognitive health. However, a traditional Mediterranean diet delivers fewer serves of dairy and less dietary calcium than is currently recommended in Australia, which may limit long-term sustainability. The present study aims to evaluate whether a Mediterranean diet with adequate dairy and calcium can improve cardiovascular and cognitive function in an at-risk population, and thereby reduce risk of cardiovascular disease (CVD) and cognitive decline. A randomised, controlled, parallel, crossover design trial will compare a Mediterranean diet supplemented with dairy foods against a low-fat control diet. Forty participants with systolic blood pressure above 120 mmHg and at least two other risk factors of CVD will undertake each dietary intervention for eight weeks, with an eight-week washout period between interventions. Systolic blood pressure will be the primary measure of interest. Secondary outcomes will include measures of cardiometabolic health, dietary compliance, cognitive function, assessed using the Cambridge Neuropsychological Test Automated Battery (CANTAB), psychological well-being and dementia risk. This research will provide empirical evidence as to whether the Mediterranean diet can be modified to provide recommended dairy and calcium intakes while continuing to deliver positive effects for cardiovascular and cognitive health. The findings will hold relevance for the field of preventative healthcare and may contribute to revisions of national dietary guidelines.

## 1. Introduction

### 1.1. Background

Worldwide, cardiovascular disease (CVD) is the leading cause of death [1], while dementia is one of the greatest contributors to disability and dependence for individuals over the age of 60 [2]. Due to population growth and demographic ageing the prevalence and cost of age-related diseases and disorders, such as CVD and dementia, will continue to rise. Dementia currently affects 46.8 million people and numbers are expected to double every 20 years and reach 131.5 million by 2050. Between 2010 and 2015 the global cost of dementia increased by 35.4% to $818 billion USD, and is predicted to reach $2 trillion USD by 2030 [2]. Similarly, projections indicate that costs associated with CVD will triple by 2030 [3,4].

CVD and dementia share common risk factors including ageing, smoking, obesity, hypertension, dyslipidaemia and diabetes mellitus. Individually and collectively, these risk factors contribute to an inflammatory process that compromises endothelial function and promotes the development of atherosclerosis [5,6]. Atherosclerotic disease is the leading cause of CVD, coronary artery disease and cerebrovascular disease, and a significant predictor of late-life dementia and Alzheimer’s disease (AD) [7,8]. 

The same risk factors may further contribute to AD and dementia through independent pathways. Hypertension, for example, is capable of altering brain structure and volume, particularly in regions of the brain vulnerable to ageing and associated with AD, such as the prefrontal cortex [9,10,11]. Together, hypertension and atherosclerosis exacerbate the already reduced cerebral blood flow associated with normal ageing [12,13], increasing the incidence of hypoxia and neuritic plaque accumulation, effectively leading to cell degeneration and death [14]. 

To alleviate the social and economic burden of CVD, recommendations have called for health and lifestyle interventions targeting multiple risk factors [8]. Furthermore, recent calculations indicate that up to one third of AD can be attributed to modifiable risk factors (such as hypertension, obesity and diabetes), and reducing these will significantly reduce the prevalence of AD [15]. 

### 1.2. Dietary Intervention

Diet is a cornerstone treatment target for primary and secondary CVD prevention [16,17]. Dietary changes (such as replacing saturated with unsaturated fats; increasing fibre, fruit and vegetable intake; reducing salt and discretionary food intake; and restricting total energy intake) have been effective for the treatment of obesity, hypertension, hyperglycaemia and dyslipidaemia [18,19,20,21,22,23,24,25,26,27,28] and may improve cognitive function and well-being [29,30,31,32,33,34,35]. Further, specific nutrients in the diet may play a positive role in cardiovascular and cognitive health. For example, the consumption of polyphenols, flavonoids and antioxidants has been linked to improvements in blood pressure, endothelial function and reductions in pro-inflammatory markers associated with atherosclerosis, such as C-reactive protein (CRP) [36,37,38,39,40,41,42]. Regular consumption of flavanols and other polyphenols has also led to improvements across the cognitive domains of processing speed, memory and global cognition in healthy adults [43,44,45,46,47], and improved cognitive performance in older adults with mild cognitive impairment (MCI) [48]. 

Individually, these dietary modifications have demonstrated positive effects on cardiovascular and cognitive outcomes. However, an integrative, whole-of-diet approach may offer further benefit.

#### The Mediterranean Diet

The Mediterranean dietary pattern is characterised by high consumption of extra virgin olive oil (EVOO), vegetables, fruit, nuts, seeds, legumes and cereals; moderate consumption of fish, poultry, dairy and red wine; and lower consumption of eggs, red and processed meat and processed foods [49]. The primary foods of the Mediterranean diet contain bioactive nutrients and phytochemicals including mono- and poly-unsaturated fatty acids such as omega-3, polyphenols including flavonoids, vitamins, minerals and fibre, arginine and antioxidants. 

Cross-sectional and prospective studies indicate that populations with higher adherence to a Mediterranean diet exhibit lower risk of CVD and AD [50,51,52,53,54]. Intervention studies examining the Mediterranean diet have reported improvements to blood pressure, lipid profiles, insulin sensitivity, CRP levels and oxidative stress [37,41,55], and amelioration of atherosclerotic disease has been observed [56]. Further, a Mediterranean diet has been shown to improve function across cognitive domains affected by dementia and AD, even after short-term interventions [57,58]. Notably, improvements in cognitive functions sensitive to dementia and AD may translate to a reduced risk or delayed onset of dementia and AD [59,60]. 

The Prevención con Dieta Mediterránea (PREDIMED) study, a long-term large-scale randomised controlled trial, examined the efficacy of a Mediterranean diet against a low-fat diet in a Spanish population at risk of developing CVD [61]. After a median follow-up period of 4.8 years, risk of CVD and incidence of major cardiovascular events was significantly reduced in groups following a Mediterranean diet compared to those following a low-fat diet. Groups following a Mediterranean diet also demonstrated improved cognitive function [62,63] and rates of MCI, a risk factor and early indicator of dementia, were significantly lower than in control group [62]. 

Improved cognitive function following consumption of a Mediterranean diet may be the result of improved cardiovascular health. For instance, reduced inflammation and improved endothelial function encourage vasodilation and cerebral blood flow, reducing oxidative stress and neuronal cell death [64]. Alternatively, constituents of the Mediterranean diet may affect brain physiology directly, as individual nutrients have been shown to influence cognitive function in isolation [65,66,67,68,69,70]. For example, long-chain omega-3 fatty acids are integral to neuronal membrane functioning [71]. Similarly, flavonoids, polyphenolic compounds obtained from fruits and vegetables, tea and red wine, have been identified for their role in protecting against oxidative stress and neuronal death [72]. 

The potential for the Mediterranean diet to improve health outcomes is significant and has been acknowledged at the level of national nutritional policy. Recent modifications to the American Dietary Guidelines, for example, now include the Mediterranean diet as a healthy eating pattern [73,74].

### 1.3. Dairy Foods 

The Mediterranean diet shows promise for the prevention of CVD and dementia. However, before the diet is recommended as a long-term intervention it is necessary to ensure that it meets the nutritional requirements of the target population. 

Notably, a traditional Mediterranean diet does not satisfy current Australian guidelines for dairy foods. The Australian National Health and Medical Research Council recommend 2.5 to 4 serves of dairy foods, such as milk, cheese and yoghurt each day for adults (depending on age and gender) [75]. In contrast, a typical Mediterranean diet only provides 1–2 serves of dairy foods per day [49]. 

Dairy foods deliver a range of essential vitamins, minerals, peptides and micronutrients. These include calcium, iodine, vitamins A, B_6_ and B_12_, riboflavin, magnesium, potassium, phosphorus and zinc. Prior analysis indicates that the Mediterranean dietary pattern, as a whole, meets Australian requirements for most of these nutrients, with the exception of zinc (due to the complex nature of the bioavailability of zinc and estimating dietary requirements) and calcium [49].

Adequate dietary calcium is essential to skeletal function and integrity [76]. This is of particular relevance to an ageing population who are at a heightened risk of bone loss, bone fracture and osteoporosis [77,78]. Adequate calcium is also vital to cognitive function, as synaptic transmission and the neuronal processes involved in learning and memory are dependent on calcium signalling [79].

Calculations suggest that calcium intake on a Mediterranean diet is approximately 700–820 mg/day [80,81]. This meets the recommended dietary intake (RDI) of 750 mg for European countries [82] but is below both the estimated average requirement (EAR) (840–1100 mg/day) and the RDI for Australians, where women up to the age of 50 and men up to the age of 70 are advised to consume 1000 mg daily, and 1300 mg thereafter [76]. Recommended daily intakes are indicative of the traditional intakes of a population, accounting for deficits and needs. The difference between Australian and European RDIs for calcium may then be a reflection of the prevalence of osteoporosis. In Australia, it is estimated that 27% of men and 44% of women over the age of 50 will develop osteoporosis [83]. In contrast, Mediterranean countries such as Greece, Italy and Spain report a lower incidence of osteoporosis: prevalence over the age of 50 ranges from 6.8%–7% for men and 22%–23.5% for women [84]. 

For the long-term sustainability of a Mediterranean diet in an Australian population it is necessary to ensure that calcium requirements are met, especially in consideration of bone health concerns. Recommending a calcium intake of approximately 700–820 mg/day, as obtained from a traditional Mediterranean diet, might not be optimal or viable for an Australian population in whom a greater calcium intake still results in higher prevalence of osteoporosis, and where habitual calcium intake of less than 751 mg/day is associated with increased risk of osteoporosis [85]. 

While the impact of dairy foods in a Mediterranean diet is currently unknown, nutrients contained in dairy foods have been identified for their potential to improve cardiovascular risk factors. For example, calcium has been linked to weight loss and improvements in lipid profiles and insulin sensitivity [86,87,88]; magnesium may be beneficial for blood pressure, insulin sensitivity and lipid profiles [88,89,90]; and phosphorus from dairy foods has been linked to reduced risk of hypertension [91]. Moreover, dairy food consumption is associated with better outcomes for blood pressure, inflammation, insulin sensitivity, and CVD [41,92,93,94,95,96]. By improving cardiovascular health, dairy foods may also be capable of improving cognitive function. Further, constituents of dairy foods, such as bioactive peptides, amino acids and vitamin B_12_ may affect brain physiology to improve cognitive function directly [97]. Despite this, clinical trials have reported both positive and negative relationships between dairy intake and cognitive functioning [98,99,100]. The potential impact of added dairy on cognition therefore requires further attention.

Increasing serves of dairy foods in the Mediterranean diet, to supply adequate calcium for an Australian population may increase endorsement, adoption and sustainability for an Australian population. However, foods are not consumed in isolation, but are instead components of a dietary pattern. It is therefore unclear whether additional dairy will compromise or work in synergy with other elements of the Mediterranean diet. 

### 1.4. Objectives

The current study aims to evaluate the effect of a Mediterranean diet that meets Australian dairy and calcium recommendations. Specifically, a Mediterranean diet supplemented with additional dairy (milk, cheese and yoghurt) will be compared with a low-fat control diet on measures of cardiovascular risk and cognitive performance, quality of life and psychological well-being. A secondary aim of the current study is to determine the extent to which intervention effects on cognitive function are dependent on improvements to cardiovascular health.

For the primary prevention of CVD, targeting individuals at high risk may be more effective than targeting those at low or medium risk [101]. To evaluate the potential of a Mediterranean diet to reduce risk, the intervention will be administered to a sample with multiple risk factors of CVD, who are therefore at high risk of CVD and premature cognitive decline. As blood pressure a modifiable and strong predictor of CVD, brain atrophy and dementia, home blood pressure will be used as the primary outcome measure. Secondary outcomes will include measures of cardiometabolic health such as diastolic blood pressure, body mass index (BMI), waist-to-hip ratio, body composition, red blood cell fatty acids, blood lipids, Apolipoprotein E4 (ApoE4), C-reactive protein (CRP), blood glucose and insulin, estimated risk of dementia and measures of cognitive function. Specifically, memory, processing speed and executive function will be examined as each of these is sensitive to age-related decline, and task performance is predictive of cognitive ageing and risk of dementia and Alzheimer’s disease [30,102,103,104,105,106,107,108]. Further, these cognitive functions are negatively affected by hypertension, endothelial dysfunction, atherosclerosis and CVD [10,103,104,109,110,111,112,113,114,115,116,117,118,119].

The findings of this research will provide insight as to whether a Mediterranean diet that meets the dairy food group and calcium requirements of the target population is still capable of reducing risk of CVD and cognitive decline.

## 2. Materials and Methods 

### 2.1. Ethics

Ethical approval has been obtained from the University of South Australia Human Ethics Committee. The trial was registered with the Australia and New Zealand Clinical Trials Registry (ACTRN12616000309482) on 9 March 2016.

### 2.2. Participants 

#### 2.2.1. Inclusion Criteria

Volunteers aged between 45 and 75 with elevated systolic blood pressure above 120 mmHg and who are not taking antihypertensive medication will be recruited. To be eligible, volunteers will have at least two other risk factors for CVD, including: a body mass index ≥25 kg/m^2^; abdominal adiposity (waist circumference >94 cm for men and >80 cm for women); elevated total cholesterol (≥5.5 mM), triglycerides (≥2.0 mM), low-density lipoprotein (LDL) (≥3.5), or low levels of high-density lipoprotein (HDL) (≤0.9 for men and ≤1.0 for women); impaired glucose tolerance (between 6.1 and 7.8 mmol/L); and/or a family history of CVD or type 2 diabetes. 

#### 2.2.2. Exclusion Criteria 

Current smokers, individuals with medical conditions including: current CVD or angina, current or recent malignancies, kidney disease, gastrointestinal disease, respiratory disease, Type 2 diabetes mellitus, a current or previous traumatic head or brain injury, a current neurological or psychiatric condition, or a current diagnosis of Alzheimer’s disease or dementia will be excluded from participation. Volunteers with dietary requirements, aversions, allergies or intolerances, such as fish and nut allergies or lactose intolerance, that will interfere with their ability to follow dietary guidelines will not be invited to participate. Further, individuals taking medicinal levels of calcium or >1000 mg of omega-3 supplements daily will not be eligible. 

#### 2.2.3. Recruitment and Screening

Volunteers will be recruited through electronic and paper media advertisements and assessed for eligibility through a diet and lifestyle questionnaire (DLQ) and screening visit at the Sansom Institute Clinical Trial Facility. The DLQ will include questions regarding medical history, medications and supplements, family medical history, dietary requirements, aversions, allergies and intolerances. At the screening visit the Addenbrooke’s Cognitive Exam-Revised (ACE-R) [120] will be administered to detect pre-existing MCI and dementia. Blood pressure will be measured as detailed below, in addition to anthropometry (height, weight, waist and hip measurements), fasting blood glucose using a finger-prick glucose test. A fasting blood sample will also be collected to measure blood lipid profile.

### 2.3. Design

The current study will employ a 24-week 2 × 2 crossover design. Participants will complete two 8-week dietary interventions, separated by an 8-week washout period. Participants will be allocated to a starting diet group, either the Mediterranean diet or the low-fat diet, using block randomisation and stratification based on age and gender. In Phase 1, participants will follow their starting diet for 8 weeks. All participants will then return to their habitual diet for 8 weeks, after which they will “cross-over” and complete the second 8-week intervention for Phase 2 (see Figure 1). All participants will therefore complete each experimental condition. 

The crossover design has been chosen for time and resource efficiency. As participants will act as their own control, potential differences between subjects in both observed and unobserved confounders that may be present in a medium-sized parallel-group design will be removed. This will reduce the potential for bias in estimating the treatment effect. In addition, repeat measures on the same individual allows for separate estimation of the true underlying value for each individual, the treatment effect and the measurement error. Separating the treatment effect from the measurement error will allow a more precise estimation of the treatment effect and fewer participants will therefore be required to detect any between-group differences. The reduced bias due to the removal of potential confounding variables will also enhance the internal validity of the design. An 8-week intervention period is expected to be adequate as similarly timed RCTs have demonstrated significant effects of nutrients contained in the Mediterranean diet, such as flavanols and omega-3s, on cardiovascular outcomes [46,48,121]. Further, the observed changes in cardiovascular outcomes were found to mediate improvements in cognitive function. As there is the potential for latency effects beyond 8 weeks, Potential carry-over effects will be assessed by testing for treatment × phase interactions, and it is anticipated that 8 weeks will be an adequate washout period to prevent cross-contamination between intervention phases [109]. Practice effects of cognitive tasks will be mitigated through the use of measures with strong test-retest reliabilities, counterbalancing of test order and the use of multi-level analysis that will allow the separation of measurement error (i.e., within-subject variability) from treatment effects.

### 2.4. Dietary Interventions

Weight loss has been linked to significant reductions in systolic and diastolic blood pressure, blood glucose, triglycerides and total cholesterol and inflammatory markers [122,123], as well as improvements to cognitive function [124], and so has the potential to mask the effects of a nuanced dietary intervention. To measure the effects of the intervention independent of weight loss, energy will not be restricted. Instead, participants will be instructed to consume all dietary interventions ad-libitum and self-regulate their food intake. If weight loss occurs the volunteer will be counselled to ensure that they are eating until satiated and that all dietary serving requirements are met. If weight loss continues changes in weight within each phase will be adjusted for statistically.

#### 2.4.1. The Low-Fat Diet (LFD)

Modelled on the PREDIMED study, participants will follow their habitual diet but will be instructed to reduce their total fat intake by restricting or avoiding intakes of high fat foods including all oil types, butter, margarine, full fat dairy, processed and high fat meats, cream, nuts, chocolate, cakes, biscuits, pastry and ice cream. Participants will be instructed to replace these foods with low fat alternatives such as breads, cereals, lean meats, legumes, rice, vegetables and fruits, or by choosing low fat variations (such as low fat dairy). Participants will be advised to consume no more than 20 mL of oil, no more than two teaspoons butter or margarine per day, and to remove visible fat and skin from meat and fish before cooking. As the LFD is intended to match participants’ habitual dietary intakes, recommendations will not be set for dairy consumption.

#### 2.4.2. The Mediterranean Diet Supplemented with Dairy (MedD)

While following the MedD intervention, participants will be instructed to adhere to the following guidelines (adapted from Estruch, Ros, Salas-Salvadó, Covas, Corella, Arós, Gómez-Gracia, Ruiz-Gutiérrez, Fiol, Lapetra, Lamuela-Raventos, Serra-Majem, Pintó, Basora, Muñoz, Sorlí, Martínez and Martínez-González [61] for Australian food supply):
3–4 daily servings of dairy foods (one serve = 250 mL low fat milk, 40–120 g hard and/or semisoft to soft cheese, 200 g low fat Greek yoghurt, or 200 g tzatziki dip);No more than one serving of cheese (any type) per day (one serve = 40 g hard, 50 g semi-soft, or 120 g soft cheese);Minimum of one tablespoon (20 mL) of EVOO per day;≥2–3 daily servings of fresh fruit (one serve = 150 g fresh, 40 g dried, or one cup canned in juice);≥3 weekly servings of legumes (one serve = 75 g);≥3 weekly servings of fish and seafood (at least one serving of oily fish) (one serve = 100 g cooked);≥3 weekly serving of nuts or seeds (one serve = 30 g; 7.5 g hazelnuts, 15 g walnuts, 7.5 g almonds supplied for each serve);Ad-libitum consumption of wholegrain cereal products (bread, pasta, rice, cereal), nuts, fish, eggs and raw and cooked vegetables;Select white meats (poultry without skin) instead of red meats or processed meats;Limit consumption of red meat (remove all visible fat), cured ham and chocolate to ≤1 serve/week (one serve of red meat/cured ham = 100 g; one serve of chocolate = 50 g);Use EVOO for cooking and dressing vegetables and salad;Cook regularly (at least twice a week) with a tomato based sauce (EVOO, tomato, garlic and onion);Dress vegetables, pasta, rice and other dishes with EVOO, tomato, garlic and onion sauce;Eliminate or limit the consumption of cream, butter, margarine, cold meat, pate, duck, carbonated and or sugared beverages, pastries, commercial bakery products (cakes, donuts, cookies), desserts (puddings), French fries, potato crisps, sweets;For usual drinkers, red wine is recommended as the main source of alcohol with a maximum of two standard drinks per day (200 mL = two standard drinks) [125].

Consistent with Australian Dietary Guidelines [75], serving sizes of dairy foods will deliver 300 mg of calcium. Three to four servings of dairy each day will therefore provide approximately 900 to 1200 mg of calcium, while vegetables and nuts will provide approximately 100 mg. Based on this modelling, the MedD diet will provide 1000–1300 mg of calcium each day, and thus meet the Australian RDI for calcium.

Although recommended for the control of blood pressure, restriction of dietary sodium is not a component of the Mediterranean diet and thus participants will not be instructed to reduce salt intake. 

To assist with adherence, the following foods will be provided: Chobani Greek yoghurt (donated by Chobani Australia Pty Ltd., Dandenong South, Victoria, Australia), almonds (donated by the Almond Board of Australia, Loxton, Australia), walnuts and hazelnuts, EVOO (donated by Cobram Estate, Southbank, Victoria, Australia), Mainland Tasty regular fat and reduced fat cheese slices (donated by Fonterra Co-Operative Group, Darnum, Victoria, Australi), Edgell chickpeas, cannellini beans, red kidney beans, 4-bean mix and lentils (donated by Simplot Australia Pty Ltd., Rose Park, Australia) and canned John West tuna “tempters” and salmon “tempters” (donated by Simplot Australia Pty Ltd.). 

Adverse effects of the Mediterranean diet may include constipation, diarrhoea and bloating due to a high intake of fibre. Participants will be encouraged to discuss any adverse effects during dietetic counselling sessions, in which the dietitian will offer advice to minimise discomfort. 

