##### Diet Adherence

Adherence to the MedD intervention will be assessed using the weekly checklist (Appendix C, described above). Weekly totals of each food group will be compared against dietary guidelines to determine % adherence to the MedD diet. A 14-item Mediterranean diet adherence tool, adapted from the PREDIMED study to align with the Australian food supply and The Australian National Health and Medical Research Council (NHMRC) guidelines for alcohol consumption, will also be completed and returned at each fortnightly visit [61] (Appendix F). Adherence to the LFD will be measured using a 9-item low-fat diet adherence tool adapted from the PREDIMED study, completed and returned at each fortnightly visit [61] (Appendix G). These tools are designed to capture a generalised pattern of consumption relevant to the dietary phase. Finally, a 6-day weighed food record (WFR) will be completed before and during each dietary phase to calculate energy and macro and micronutrients intakes. 

Adherence to the whole dietary phase and the dairy food component of the MedD intervention will be determined at the first fortnight dietetic visit. Participants must meet a minimum of 75% adherence (as determined by checklists) to the relevant dietary prescription and a minimum of 75% adherence to the dairy recommendation (i.e., participants need to consume at least 3 serves dairy products per day to be compliant). If participants are unable to increase adherence above 75% in the next fortnight they will be excluded from the study.

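### The MedD diet is said to meet the Australian calcium RDI, but at the 3 dairy serves that count as compliant the protocol's own model gives 1000 mg, short of the 1300 mg RDI for women over 50 and men over 70

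*Protocol article*

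**What the plan says.** The protocol article treats calcium adequacy in five places.

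- **Section 1.3 (Dairy Foods)** gives the Australian RDI by age and sex: "women up to the age of 50 and men up to the age of 70 are advised to consume 1000 mg daily, and 1300 mg" above those ages.
- **Section 2.2.1 (Inclusion Criteria)** admits "Volunteers aged between 45 and 75", with no restriction by sex.
- **Section 2.4.2 (MedD diet)** prescribes 3–4 dairy serves a day, one range for all participants. Its model of the calcium supply assumes that "serving sizes of dairy foods will deliver 300 mg of calcium". On that basis dairy is put at 900–1200 mg a day, and the only other sources counted are vegetables and nuts, at about 100 mg. From this it concludes that "the MedD diet will provide 1000–1300 mg of calcium each day, and thus meet the Australian RDI for calcium".
- **Section 2.5.2, Diet Adherence**, sets a 75% minimum for the dairy component and spells out what that means: "participants need to consume at least 3 serves dairy products per day to be compliant". The threshold is the same for every age and sex.
- The same subsection's **modified 15-point Mediterranean score** awards its dairy point at 3 or more serves a day, again for everyone.

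Section 1.4 (Objectives) makes adequacy the defining feature of the intervention: the trial is to evaluate a Mediterranean diet that satisfies Australian dairy and calcium recommendations.

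**The concern.** The RDI sentence in section 2.4.2 compares a range of intakes with a single RDI, whereas section 1.3 gives two. For the groups with the higher value, the claim is true only at the top of the prescribed range. The rules that decide who is compliant, and who scores the dairy point, are set at the bottom of it.

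This matters for interpretation. The introduction justifies the trial by arguing that the traditional Mediterranean diet falls short of the Australian calcium RDI, and the objectives ask whether a diet without that shortfall still works. A woman over 50 or a man over 70 can pass the stated dairy checks and still, on the protocol's model, not be on a diet that meets the RDI. A report that the tested diet met calcium recommendations would then claim something the compliance rule does not secure. The abstract says the findings may feed into revisions of national dietary guidelines, so the wording of that claim has consequences.

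**Working it through.** **Inputs (all from the protocol article)**

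- Calcium per dairy serve: 300 mg (section 2.4.2)
- Non-dairy calcium in the model: about 100 mg, from vegetables and nuts (section 2.4.2)
- Prescribed serves: 3–4 per day (section 2.4.2)
- Compliance threshold: 3 serves per day (section 2.5.2, Diet Adherence)
- RDI: 1000 mg for women up to 50 and men up to 70; 1300 mg above those ages (section 1.3)
- Eligible ages: 45 to 75 (section 2.2.1)

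**Step 1. Reproduce the stated range.** Modelled calcium = serves × 300 + 100.

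- 3 serves: 3 × 300 + 100 = 1000 mg
- 4 serves: 4 × 300 + 100 = 1300 mg

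This matches the stated 1000–1300 mg exactly.

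**Step 2. Compare with each RDI.**

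| Serves per day | Modelled calcium | Against 1000 mg | Against 1300 mg |
|---|---|---|---|
| 3 | 1000 mg | met, no margin | 300 mg short (300/1300 = 23%) |
| 3.5 | 1150 mg | met | 150 mg short |
| 4 | 1300 mg | met | met, no margin |

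Serves needed for 1300 mg on this model: (1300 − 100)/300 = 4.0, the top of the prescribed range.

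**Step 3. Check the compliance rule.** 0.75 × 4 = 3, so the 3-serve threshold is 75% of the top of the range. For anyone with the 1300 mg RDI, it accepts a modelled intake 300 mg below that RDI.

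**Step 4. Who has the higher RDI.** The article gives no age or sex distribution. As an illustration, assume ages spread evenly over 45–75. The 1300 mg RDI then applies to 25/30 = 83% of women and 5/30 = 17% of men. For the whole sample:

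- 30% women: 0.30 × 25/30 + 0.70 × 5/30 = 37%
- 50% women: 0.50 × 25/30 + 0.50 × 5/30 = 50%
- 70% women: 0.70 × 25/30 + 0.30 × 5/30 = 63%

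These are shares with the higher RDI, not shares falling short of it.

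**Step 5. How firm is the 1000 mg?** The model's 100 mg covers vegetables and nuts only, although the MedD diet also includes legumes, fish, fruit and cereals. Section 1.3 puts total calcium on a traditional Mediterranean diet at 700–820 mg with 1–2 dairy serves. Assume those serves also carry 300 mg each. Non-dairy calcium would then be between 700 − 600 = 100 mg and 820 − 300 = 520 mg. Intake at 3 serves would be between 900 + 100 = 1000 mg and 900 + 520 = 1420 mg. The modelled 1000 mg is thus the low end of what the article's figures allow, and whether 3 serves reach 1300 mg in practice is open.

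**The case against.** The strongest defence is that the two ends of the modelled range equal the two RDI values. The authors may have intended 3 serves for the lower RDI and 4 for the higher. Section 1.3 notes that national dairy recommendations vary with age and gender, and the participant guidance in Appendices A and B is not shown. A compliance floor is also a tolerance, not the prescription. This is fair as a reading of intent, and tailoring in the appendices cannot be excluded. It does not rescue the claim: even with a tailored prescription, Diet Adherence would count a participant with the 1300 mg RDI as compliant at 3 serves.

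A second defence is that real intake probably exceeds the model. That stands as a limit on the size of the shortfall. But section 2.4.2 rests its RDI statement expressly on this modelling, so the statement has to hold on it.

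A third is that the weighed food records will already yield micronutrient intakes, and section 2.7 compares these between diets. That makes the remedy cheap, but a comparison between diets does not show who met their own RDI.

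Stronger conclusions are tempting, and the article does not support them:

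- A reader might take 75% adherence as 75% of 3 serves, that is 2.25 serves or 775 mg, no better than the traditional diet. The explicit gloss in Diet Adherence fixes the threshold at 3 serves. Moreover, 775 mg counts only dairy, vegetables and nuts, so it cannot be set against a whole-diet intake of 700–820 mg.
- A reader might note that 1000 mg is below the 1100 mg top of the quoted EAR range (840–1100 mg). Section 1.3 does not assign that range by age or sex, so nothing firm follows.
- A reader might infer that half or more of the sample will miss the RDI. The shares in the working rest on assumed age and sex mixes, and they count people with the higher RDI whatever they eat.
- A reader might infer that the main trial result is compromised. It is not: the primary comparison is home systolic blood pressure between the two diets.

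**Conclusion.** The point holds as a contradiction within the protocol. The unqualified statement that 3–4 serves meet the Australian RDI is not true, on the protocol's own figures, for women over 50 and men over 70 at the 3 serves that count as compliant. The modelled gap is 300 mg a day, 23% of the 1300 mg RDI, and it closes only at 4 serves.

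This rests on the protocol's model of 300 mg per serve plus about 100 mg, which may understate real intake. How many participants are affected cannot be known from the document: under an even age spread, the higher RDI would apply to about 37% of the sample at 30% women and 63% at 70% women. The consequence is confined to how the intervention is described and what may be concluded about calcium adequacy. Sample size, randomisation and the primary blood pressure analysis are untouched.

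**What to change.** 1. Reconcile section 1.3 (the two RDIs), section 2.4.2 (the prescription and the RDI claim) and section 2.5.2, Diet Adherence (the compliance threshold and the dairy item of the 15-point score), so that the claim and the compliance rule refer to the same age- and sex-specific figure. Which serving rule applies is for the sponsor to decide.
2. From the 6-day weighed food records already collected, report the proportion of participants who met the RDI for their own age and sex during the MedD phase.
3. Limit any conclusion that the diet meets calcium recommendations to what those records show.

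The cost is a change of wording and one additional table, with no new data collection. The downside is that the claim about the diet may become narrower than the protocol now states it.
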